### Sample size

For comparing different interventions among the four groups, the sample size is computed through the STATA software using a standard deviation of 18.5 in systolic blood pressure taken from a Pakistani study [9], population means of 148 and 143 respectively, as 5 mmHg reduction in systolic blood pressure is related to clinical importance regarding decreasing the risk of coronary artery disease [25]. A two-sided level of significance of 5% and a power of 90% with a 30% attrition rate between the baseline and 12 months of the intervention period were used. The total sample size calculated is 1648 with 412 in each group.

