### Statistical analysis

The intention-to-treat analytic method will be conducted [35, 36]. Mixed-effects modeling with repeated measures will be employed for the primary outcome change in systolic blood pressure at 0, 6, and 12 months. To estimate treatment effects at each time point, an interaction between time and the groups will be fitted. For the primary and secondary outcomes measuring systolic blood pressure and medication adherence difference between and with the group at 0, 6, and 12 months, parametric (ANOVA/repeated measure ANOVA) and non-parametric tests *(*Kruskal*-*Wallis test*/*Friedman test/Wilcoxon signed*-*rank test) will be used. We shall account for the multiple time points statistically by using Tukey’s exact test. The Tukey test will be utilized for multiple comparisons and adjustment for multiple comparisons will be performed by Bonferroni correction. All the outcomes will be analyzed at 0, 6, and 12 months; however, the final analysis will be at 12 months from baseline. The *p*-value for the significance test will be set at *p* < 0.05. Pill counting data, adherence assessment at dichotomous variables, frequencies, and the chi-square test will all be used. By using the general estimating equation (GEE) with negative binomial regression, at 12 months post-follow-up, the covariates affecting primary and secondary outcomes including, age, gender, ethnicity, living status, education, monthly income, use of reminder, health insurance coverage, body mass index (BMI), diabetes, duration of illness, number of comorbid conditions, number of daily medication use, dose frequency will be determined and controlled. A complete analysis plan will be established for data analysis, including subgroup analyses and sensitivity analyses.

Sub-group analyses of the change in systolic blood pressure, the adherence to medication over the previous 12 months will be conducted by age (21–29 years, 30–49 years, 50 years and above), sex (male, female), adherence (SEAMS, pill-counting), and health-related quality of life (using EQ-5D-3L and EQ-VAS). Missing data from attrition will be handled using a multiple imputations approach at 12 months.

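### The stated 90% power belongs to one unadjusted two-arm comparison; for the multiplicity-adjusted four-group comparisons that the plan describes, the same inputs give about 73 to 80%

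*Protocol article*

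**What the plan says.** The Sample size section presents the calculation as serving the four-group question: "For comparing different interventions among the four groups, the sample size is computed". Its inputs describe two groups only: "population means of 148 and 143 respectively, as 5 mmHg reduction in systolic blood pressure is related to clinical importance", and "using a standard deviation of 18.5 in systolic blood pressure taken from a Pakistani study". The error rates and the attrition allowance are "A two-sided level of significance of 5% and a power of 90% with a 30% attrition rate between the baseline and 12 months". Nothing in the section mentions multiplicity.

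The first research objective asks for mean differences in systolic blood pressure among all four groups. For the tests, the Statistical analysis section states: "The Tukey test will be utilized for multiple comparisons and adjustment for multiple comparisons will be performed by Bonferroni correction". It does not give the number of comparisons, and it does not say whether the two methods are alternatives or are applied together. On repeated visits it adds "We shall account for the multiple time points statistically by using" a Tukey procedure. The same section places the final analysis at 12 months and plans a mixed model with a group-by-time interaction for the primary outcome.

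**The concern.** Power belongs to a particular test at a particular threshold. The sample size was worked out for one comparison at two-sided 5%. Under any reading of the multiplicity sentence, each pairwise comparison faces a stricter threshold, so the power quoted in one section is not the power of the comparisons described in the other.

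Two further faults lie in the multiplicity rule itself.

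- Tukey's range test already controls the family-wise error over all pairwise group comparisons. A Bonferroni correction on top of it would correct twice.
- The range test is built for independent groups. It does not suit repeated measurements in the same participants.

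At stake is whether a true effect of 5 mmHg, the size the protocol calls clinically important, would be declared significant. Two analysts could also follow the same text and reach different conclusions on the primary outcome.

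**Working it through.** **Inputs**, all from the Sample size section: difference 148 − 143 = 5 mmHg; SD 18.5 mmHg; two-sided alpha 0.05; power 90%; attrition 30%; 412 per group, 1648 in total.

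**Step 1: reproduce the plan's figure.**

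- n per arm = 2 × (1.960 + 1.2816)² × 18.5² / 5² = 287.7, rounded up to 288 evaluable.
- 288 / 0.70 = 411.4, rounded up to 412.
- 4 × 412 = 1648.

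This matches exactly. The stated size is one unadjusted two-sample calculation repeated over four arms.

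**Step 2: power under adjusted thresholds.**

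- Standard error of a pairwise difference = 18.5 × √(2/288) = 1.542 mmHg.
- Standardised effect = 5 / 1.542 = 3.243.
- Power = Φ(3.243 − critical value).
- Difference detectable at 90% power = (critical value + 1.2816) × 1.542.

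The Bonferroni critical values are normal quantiles at 0.05/3 and 0.05/6, two-sided. The Tukey value is the studentized range quantile for four groups (1148 degrees of freedom) divided by √2. The stacked row uses the same quantile at family level 0.05/6.

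| Rule | Critical value | Power at 5 mmHg | Detectable at 90% |
|---|---|---|---|
| Unadjusted | 1.960 | 90.0% | 5.0 mmHg |
| Bonferroni, 3 comparisons with standard care | 2.394 | 80.2% | 5.7 mmHg |
| Tukey, 6 pairs | 2.573 | 74.9% | 5.9 mmHg |
| Bonferroni, 6 pairs | 2.638 | 72.7% | 6.0 mmHg |
| Tukey, then Bonferroni for 6 pairs | 3.176 | 52.7% | 6.9 mmHg |

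The number of comparisons is an assumption, because the protocol does not give it. Six is every pair of four groups and fits the four-group objective. Three fits the abstract's aim of comparing the modules with standard care.

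**Step 3: size that would restore 90%**, with the same formula and the same division by 0.70.

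| Rule | Evaluable per arm | Recruited per arm | Total |
|---|---|---|---|
| Bonferroni, 3 | 370 | 529 | 2116 |
| Tukey, 6 | 407 | 582 | 2328 |
| Bonferroni, 6 | 421 | 602 | 2408 |
| Both stacked | 545 | 779 | 3116 |

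**Step 4: what baseline adjustment would have to deliver.** If the variance falls by a factor 1 − ρ², where ρ is the correlation between baseline and 12-month pressure, 288 per arm gives 90% when 1 − ρ² = 288 / (evaluable number needed). For Tukey, 288/407 = 0.708, so ρ is about 0.54. For Bonferroni over six pairs, 288/421 = 0.684, so ρ is about 0.56. For both stacked, 288/545 = 0.528, so ρ is about 0.69. The protocol gives no correlation.

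**The case against.** The strongest reply has four parts.

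- **Baseline information.** The primary analysis is a repeated-measures mixed model, which may use baseline values and recover power. This is fair, and a correlation of about 0.54 to 0.56 would be enough for six pairs under one correction. But the Sample size section claims no such gain and gives no correlation, so its 90% cannot rest on one.
- **Another kind of power.** Tukey and Bonferroni can be read as follow-up tests after an omnibus test. If all three active arms lie at 143 and standard care at 148, the four-group ANOVA has 93% power, and the chance that at least one comparison with standard care is significant is about 91 to 93% with Tukey or Bonferroni over six pairs. If two arms differ by 5 mmHg and the other two lie midway, omnibus power is 78%. The protocol specifies none of these patterns; it gives two means, which is a pairwise calculation.
- **Stacking is the harshest reading.** This stands. A reader might infer that the plan's decision rule has 53% power, but the sentence does not say that the corrections are applied one on the other. That figure is a worst case. Nor is 73% the power of the two methods combined; it is Bonferroni alone over six pairs.
- **Over-correction is conservative, and an analysis plan is promised.** Both are true. False positives are not inflated, and the family could be defined in the later plan. That does not make the 90% already stated correct for adjusted comparisons.

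A reader might also infer that the sample size was miscalculated. It was not; Step 1 reproduces it exactly.

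**Conclusion.** The point holds as a mismatch between two sections. The 412 per group gives 90% power for one unadjusted pairwise comparison. On the document's own inputs, no adjusted pairwise comparison considered here reaches that figure: the type II error rises from 10% to about 20% for three comparisons with standard care, to 25 to 27% for six pairs, and to about 47% if both corrections are applied.

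These figures assume SD 18.5, a true difference of 5 mmHg, 288 evaluable per arm, no gain from baseline adjustment, and a family of three or six contrasts at 12 months. They do not show that the trial must fall short, since a strong enough baseline correlation could make up the loss. They show that the stated 90% is not supported for the comparisons described. Separately, applying Bonferroni to Tukey results and using the range test for repeated visits are faults in the rule whatever the family size.

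**What to change.** In the Statistical analysis section:

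- Name the 12-month group contrasts in systolic pressure as the primary family and state how many there are.
- Keep one multiplicity method and delete the second correction.
- Delete the use of Tukey for time points, and take visit-specific effects from the group-by-time contrasts of the mixed model already planned.

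In the Sample size section, restate the power for that family: about 80% for each of three comparisons with standard care, or 73 to 75% for each of six pairs. If a gain from baseline adjustment is to be claimed, state the assumed correlation and its source.

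The cost is wording and a less favourable stated power, with no extra patients.

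A primary analysis of the two factorial main effects is an option, not a straight substitute. With 576 against 576 evaluable and alpha 0.025 each, the standard error is 18.5 × √(2/576) = 1.090. Power is then Φ(5/1.090 − 2.241), about 99%, but only if each main effect is 5 mmHg with no interaction. If the combined arm adds nothing to either module alone, the main effect is 2.5 mmHg and power is Φ(2.5/1.090 − 2.241), about 52%. It also changes the question from differences among four groups to the average effect of each module.

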### Recruitment

After the screening, the participants fulfilling the eligibility criteria will be recruited. For this purpose, a trained doctor in the department of cardiology from each teaching hospital in the study will facilitate and monitor the recruitment process. Each of these doctors will be supported by one research assistant who will act as the project’s focal person in each hospital for the entire study duration. The contact information of participants who have been recruited will be gathered and saved.

After shortlisting, participants will be briefed (written and verbally) about the study and presented with consent forms bearing the option to relinquish their participation from the study at any moment of its duration. Participants will subsequently be enrolled and assigned code numbers by the principal investigator. All these participants will be able to select their communication language of choice (Urdu and/or English), as well as the day and hour of their respective sessions.

### Randomization and blinding

To avoid any potential bias, a simple complete randomization procedure will be utilized [26]. A computer-generated, simple complete random approach will be used to divide participants into four groups [27]. To keep their identities hidden, all participants will be assigned an identification number. To keep the allocation of participants into four groups hidden from the research staff, tight concealment of allocation will be observed. Before allotment, written assignments will be sealed in opaque packets with tagged identifying numbers [28].

All subsequent randomization processes will be completed by an independent biostatistician who will no longer be a participant in the trial. Independent personnel will be involved in the randomization, evaluation, and intervention delivery. The staff involved in data collection and outcome assessment will be blinded. They will be unaware of the allocation of any group [29].

The recruitment process will continue until a final sample size of 1648 people from four teaching hospitals is reached. Participants’ follow-up period is 12 months from the point of randomization (Fig. 2).

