**Methods:**

We chose a double-blinded pragmatic randomized-controlled with factorial design for this investigation. The trial is going to recruit 1648 hypertensive patients with coronary artery disease at the age of 21 to 70 years. All participants will already be on anti-hypertensive medication and own a smartphone. They will be randomized into four groups with each having 412 participants. The first group will only receive standard care; while the second group, in addition to standard care, will receive monthly Ed-counselling (educational booklets with animated infographics and peer counseling); the third group will receive daily written and voice reminders and an education-led video once weekly together with standard care; while the fourth one gets both interventions given to second and third groups respectively. All groups will be followed-up for 1 year (0, 6, and 12 months). The primary outcome will be the change in systolic blood pressure while secondary outcomes include health-related quality of life and changes in medication adherence. For measuring changes in systolic blood pressure (SBP) and adherence scores difference at 0, 6, and 12 months between and within the group, parametric (ANOVA/repeated measure ANOVA) and non-parametric tests *(*Kruskal*-*Wallis test*/*Friedman test*)* will be used. By using the general estimating equation (GEE) with negative binomial regression, at 12 months, the covariates affecting primary and secondary outcomes will be determined and controlled. The analysis will be intention-to-treat. All the outcomes will be analyzed at 0, 6, and 12 months; however, the final analysis will be at 12 months from baseline.

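### Simple randomisation does not guarantee the stated 412 per arm and leaves hospital mix to chance, and hospital is not named in the stated adjustment

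*Protocol article*

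**What the plan says.** The Randomization and blinding section names the method twice: "To avoid any potential bias, a simple complete randomization procedure will be utilized", and then "A computer-generated, simple complete random approach will be used to divide participants into four groups". It mentions no blocks, no strata and no cap per arm. Recruitment is closed by the total alone: "The recruitment process will continue until a final sample size of 1648 people from four teaching hospitals is reached".

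Two other places give a size for each arm. The Abstract (Methods) says "They will be randomized into four groups with each having 412 participants", and the Sample size section says "The total sample size calculated is 1648 with 412 in each group".

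The Intervention section defines the comparator, which every arm also receives, as standard care according to each hospital's practice. The Recruitment section gives each hospital its own recruiting doctor and research assistant.

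The Statistical analysis section lists 14 covariates for the generalised estimating equation analysis at 12 months. The list begins "age, gender, ethnicity, living status, education, monthly income, use of reminder, health insurance coverage, body mass index (BMI), diabetes, duration of illness" and ends with three counts or frequencies (comorbid conditions, daily medications, doses). All are patient-level, and hospital is not among them. For the primary mixed model the only stated term is a time-by-group interaction.

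**The concern.** Two points need attention.

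First, the allocation method and the arm sizes do not fit together. Under simple randomisation each participant is allocated independently, so arm sizes vary. If instead a fixed list with 412 places per arm was prepared, the sizes are right but the method is misnamed. One of the two statements needs correcting.

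Second, neither method balances arms within hospitals. By the article's own account background care can differ between hospitals, so hospital may predict how systolic blood pressure (SBP) changes over the year. A chance difference in hospital mix between arms then adds noise to the comparison. Adjustment could remove that noise, but the stated analysis does not name the one design-level factor that randomisation leaves uncontrolled. Precision is at stake, not validity. Without a stated rule, the choice about centre adjustment could also be made after the data are seen.

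**Working it through.** **Inputs from the article.** Sample size section: "using a standard deviation of 18.5 in systolic blood pressure"; "population means of 148 and 143 respectively", a difference of 5 mmHg; two-sided 5% level; 90% power; 30% attrition; 1648 in total. Four hospitals.

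**1. The plan's own figure.**
- Evaluable per arm: n = 2(1.960 + 1.282)² × 18.5² / 5² = 287.7, rounded up to 288.
- With attrition: 288 / 0.70 = 411.4, rounded up to 412. Four arms give 4 × 412 = 1648. The figure reproduces.
- With 0.70 × 412 = 288.4 completers per arm, the standard error of a pairwise difference is 18.5 × √(2/288.4) = 1.54 mmHg and power is 90.1%.

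**2. Arm sizes under simple randomisation of 1648.**
- SD of one arm: √(1648 × 0.25 × 0.75) = 17.6. The 95% range is 412 ± 1.96 × 17.6, about 378 to 446.
- Probability that a given arm is exactly 412: 2.3%. Probability that all four are: about 1.5 × 10⁻⁵ (exact multinomial).
- From 200,000 simulated allocations: median smallest arm 393, median largest 432, median gap between them 40 (95th percentile 74).

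**3. Effect on power (normal approximation, 70% completers).**
- 378 against 412, so 264.6 against 288.4 completers: standard error 18.5 × √(1/264.6 + 1/288.4) = 1.575, 5/1.575 − 1.960 = 1.215, power 88.8%.
- For a given pair over simulated allocations: mean 90.0%, central 95% range 88.6% to 91.3%.
- For the two smallest arms: median 89.1%, 2.5th percentile 88.0%.

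**4. Hospital mix.** The article gives no split by hospital, so assume 412 patients from each. The expected number per arm within a hospital is 103, with SD √(412 × 0.25 × 0.75) = 8.8 and 95% range 86 to 120.

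**5. What hospital imbalance could add.** The article gives no between-hospital SD. Call it τ and assume that it is part of the 18.5. Chance imbalance contributes an SD of about τ√(2/412) to an unadjusted pairwise difference. The adjusted SD is √(18.5² − τ²).

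| Assumed τ (mmHg) | Imbalance SD (mmHg) | Adjusted SD (mmHg) | Power if adjusted |
|---|---|---|---|
| 2 | 0.14 | 18.39 | 90.4% |
| 5 | 0.35 | 17.81 | 92.1% |
| 8 | 0.56 | 16.68 | 94.9% |

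The imbalance SD compares with a standard error of 1.54 mmHg. Using 288.4 completers instead of 412 multiplies it by √(412/288.4) = 1.195, giving 0.17, 0.42 and 0.67.

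**6. Which scale τ is on.** The primary outcome is change in SBP. A stable hospital difference in SBP level appears at months 0, 6 and 12 alike and largely cancels from the time-by-group contrast. Only hospital differences in change remain, so τ in the table has to be read as a between-hospital SD of change. A hospital main effect alone would remove little of it.

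**The case against.** A planned arm size is often quoted beside simple randomisation as shorthand for the expected size, and no planned analysis needs equal arms. The article also has assignments prepared in advance and sealed in numbered packets, which would fit a fixed list. This stands, and it reduces the first point to wording. The wording still needs correcting, because the article states both the method and the sizes and they do not agree.

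The hospital term may be in a document that is not shown. The covariate list is introduced in a way that need not be exhaustive, a complete analysis plan is promised, and the random effects of the mixed model are not specified. Hospital was not a stratification factor, so the design does not oblige adjustment. This also stands. All that can be said is that nothing stated in the article adjusts for hospital, and that so long a list is a natural place for it.

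Two inferences should be resisted. A reader might infer that the method cannot give 412 per arm and so undermines the 90% power. Exact equality is possible though very unlikely, and typical inequality moves power by only one or two points. A reader might also infer that the counselling staff differ between hospitals. The article says only that doctors specialised in hypertension lead the sessions.

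**Conclusion.** The point holds as a modest one. The named allocation method does not guarantee 412 per arm, it leaves hospital mix to chance, and hospital is missing from the stated covariates and model term although standard care is hospital-specific.

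The arm-size results follow from the article's own figures. Pairwise power stays at about 88.6% to 91.3%, and the required total of 1648 does not change. The hospital results rest on three assumptions: equal recruitment by hospital, a between-hospital SD of change of 2 to 8 mmHg, and that this variation lies within the 18.5. On those assumptions adjustment raises power from 90.1% to between 90.4% and 94.9%. If hospitals differ in SBP level but not in change, the gain is close to nil.

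The documents do not support a reading that the treatment comparison is biased or the trial underpowered for this reason.

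**What to change.** 1. Add hospital to the adjustment list. In the primary mixed model, include hospital as a fixed effect with a hospital-by-time term, so that the adjustment acts on the change comparison. Add hospital to the secondary models. Record this before the 12-month analysis. With four hospitals and three visits the primary model spends 3 + 3 × 2 = 9 degrees of freedom, which is negligible at this size.

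2. Describe 412 as the expected arm size. If a fixed list of 412 per arm was used, correct the name of the method in Randomization and blinding instead. The cost is one sentence.

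3. Only if allocation is still open, use permuted blocks of varying size stratified by hospital. The Trial status section has recruitment ending by April 2023, before the article appeared in July 2023, so this may no longer be possible. With blocks of at most 8, arm totals could differ by at most 2 per hospital and 8 overall, against a median gap of 40 now. The cost is a new computer-generated list and slightly more predictable assignments, which varying block sizes and sealed packets limit.

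Items 1 and 2 do not depend on recruitment, and none of the three changes the sample size.
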